### Qualitative evaluation

The primary outcome relates to the effect of prognostic counselling on satisfaction with the decision-making process and proactive care planning. This includes end-of-life discussions on preferred place of death and wishes for palliative sedation and euthanasia. It will be assessed through interviews conducted with patients in cohort 2 after they receive counselling using the model.

### Statistical analysis

#### Clinical study

All values of the variables will be described separately for the control (cohort 1) and intervention group (cohort 2). The values will be expressed as mean ± SD, mean (25th to 75th percentile), or percentage, depending on the variable. Statistical analyses will be performed using the Statistical Package for the Social Sciences and R software. Missing data will be imputed using multiple imputation [42]. 

The DCS is a validated 16-item 5-point Likert-scale measurement for assessing patients’ uncertainty regarding their medical decision. It consists of five subscales measuring: uncertainty, feeling un/informed, values clarity, support and effective decision [39]. The overall score of the DCS ranges from 0 to 100. Higher scores indicate higher decision-related distress. Scores < 25 are associated with implementing decisions, while scores > 37.5 are associated with decision delay or feeling unsure about implementation [39]. Several studies suggest a total score of ≥ 25 as a cut-off for clinically significant decisional conflict [43, 44]. Both total and subscale DCS scores will be calculated in both cohorts. Additionally, the percentage of patients with clinically significant decisional conflict will be calculated.

The differences between control (cohort 1) and intervention group (cohort 2) will be tested by a T-test if the data is normally distributed. If the data is not normally distributed, the Mann-Whitney U test will be used. We will also evaluate the difference in the proportion of patients with clinically significant decisional conflict between cohort 1 and 2 using the chi-square test.

Furthermore, univariable and multivariable analysis will be performed to determine the relationship between e.g. various patient characteristics and the DCS. We will assess the independent contributions of potential influencing factors, such as smoking behaviour, level of education, marital status, age, WHO-performance status, and tumour characteristics, using multivariable regression analysis for the total DCS score and Cox-regression for survival analysis.

The overall survival function in both cohorts will be analysed using the Kaplan-Meier method. Statistical significance will be assessed using the log-rank test. Other secondary outcomes will be analysed using various tests, depending on whether the variable is continuous or categorical and whether it is normally distributed. A p-value of < 0.05 will be considered statistically significant for all analysis.

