**Methods:**

This study will employ both quantitative and qualitative approaches. The primary outcome is decisional conflict and satisfaction with the decision-making process after counselling without (cohort 1) and with (cohort 2) OncologIQ Palliative. Therefore, a prospective sequential cohort study will be conducted. Secondary outcomes include the amount of palliative treatment, overall survival rates, and quality of life. These measurements will be collected after the intervention. Additionally, patients’ perspectives on the decision-making process and proactive care planning, including end-of-life discussions, will be explored through interviews.

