To measure decisional conflict, patients will be asked to complete the Decisional Conflict Scale (DCS) questionnaire two weeks after the consult in which they received counselling. This can be done either online or by telephone. Therefore, the DCS is integrated into Healthcare Monitor, our electronic system for measuring patient-reported outcome measures (PROMs), enabling us to digitally send it to patients [37]. Data on QoL will be obtained using the EORTC QLQ-C15-PAL questionnaire, which is already included in Healthcare Monitor and is also part of our standard care for all patients with HNSCC in the palliative phase. The patient and tumour characteristics, such as smoking behaviour, ACE-27, and WHO-performance status will be collected at baseline. Additionally, data on palliative treatment, palliative sedation or euthanasia and overall survival will be gathered from the electronic patient files (EPFs).

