### Timeline

All patients will be actively participating for 1–2 months. During this period, they will complete the EORTC QLQ-C15-PAL questionnaire every 6–8 weeks, the DCS questionnaire 2 weeks after counselling, and possibly participate in an interview 3–4 weeks after counselling. Following this period, patients will no longer be actively involved in the study, as we will gather additional data from the EPF. This data will be collected from every patient over the course of the study (See Figs. 1 and 2 for an overview of the different steps and timeline).

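### The multiple-imputation rule does not separate death from non-response, and the quality-of-life comparison has no stated baseline and a schedule that does not fit its window

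*Protocol article*

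**What the plan says.** All references are to the protocol article.

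- **Missing data** (Statistical analysis, Clinical study): "Missing data will be imputed using multiple imputation". The sentence does not say which variables it covers and does not mention death.
- **QoL schedule** (Timeline): "All patients will be actively participating for 1–2 months", and in that period "they will complete the EORTC QLQ-C15-PAL questionnaire every 6–8 weeks". Afterwards, "patients will no longer be actively involved in the study, as we will gather additional data from the EPF".
- **Timing of secondary outcomes** (Abstract, Methods): "These measurements will be collected after the intervention". The variables that Recruitment and study procedures gives as examples of baseline data do not include QoL.
- **Source of QoL data** (Recruitment and study procedures): the QLQ-C15-PAL is collected through Healthcare Monitor and "is also part of our standard care for all patients with HNSCC in the palliative phase".
- **Analysis of QoL** (Statistical analysis, Clinical study): "Other secondary outcomes will be analysed using various tests, depending on whether the variable is continuous or categorical and whether it is normally distributed". Multivariable models are named only for the total DCS score and for survival.
- **Survival** (Background and rationale): the median is five months, and individual survival runs from one week to two years.

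**The concern.** A QoL score that is absent because the patient did not answer exists in principle and can sensibly be imputed. A score that is absent because the patient has died does not exist. An imputation model fitted to observed forms would fill it from the answers of survivors. If the two cohorts differ in mortality or case mix, such filled-in values can distort the QoL contrast, and survival is itself compared between the cohorts.

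The missing baseline adds to this. The cohorts are recruited one after the other, without randomisation and by different routes: patients in cohort 2 are told about the study only if they were counselled with the model. A post-counselling difference in QoL could have been present before counselling. Adjustment is stated for DCS and survival but not for QoL.

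Finally, the Timeline describes a repeated questionnaire inside a window that is barely longer than one interval, so it is unclear which forms the comparison uses.

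**Working it through.** The article gives no expected number of deaths or of QoL forms, so there is no figure of its own to reproduce on this point.

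**Step 1: forms in the active window.** One month is 365.25 / 12 / 7 = 4.35 weeks, so 1–2 months is 4.3 to 8.7 weeks. Counting from counselling:

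| Active window | Follow-up forms at a 6-week interval | Follow-up forms at an 8-week interval |
|---|---|---|
| 1 month (4.3 weeks) | 0 | 0 |
| 2 months (8.7 weeks) | 1 | 1 |

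A second follow-up form would fall at weeks 12 to 16, outside the window.

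**Step 2: deaths before each assessment.** Inputs are the median of five months (Background and rationale) and 80 patients per cohort (Sample size and power calculations). Two things are assumed: an exponential survival curve, and a clock that starts at counselling.

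P(dead by t) = 1 − exp(−ln 2 × t / 5), with t in months.

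- Week 2 (DCS): t = 0.46, so 1 − 0.938 = 6.2%, about 5 of 80.
- Week 6 (QoL): t = 1.38, so 1 − 0.826 = 17.4%, about 14 of 80.
- Week 8 (QoL): t = 1.84, so 1 − 0.775 = 22.5%, 18 of 80.

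**Step 3: sensitivity to the assumptions.**

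| Assumption | Week 2 | Week 6 | Week 8 |
|---|---|---|---|
| Exponential, median 3 months | 10.1% | 27.3% | 34.6% |
| Exponential, median 5 months | 6.2% | 17.4% | 22.5% |
| Exponential, median 7 months | 4.5% | 12.8% | 16.7% |
| Weibull shape 0.8, median 5 months | 9.8% | 21.9% | 26.8% |
| Weibull shape 1.5, median 5 months | 1.9% | 9.6% | 14.3% |

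For QoL, the exponential range is 12.8% to 34.6%, or about 10 to 28 of 80 (0.128 × 80 = 10.2; 0.346 × 80 = 27.7). If the hazard is low at first and then rises (Weibull shape 1.5), the week-6 figure falls to about 10%.

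**Step 4: the rule against the data.** The imputation sentence makes no distinction by reason for absence. Applied literally to a form due at week 6 or 8, it would cover these deaths as well as non-response. Nothing in the article excludes that, and nothing prescribes it.

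**Step 5: baseline.** The Abstract places the secondary measurements after the intervention, the baseline examples omit QoL, and the adjusted models stop at DCS and survival. Yet the questionnaire is routine care in this population, so an early form may already exist for many patients.

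**The case against.** Several stronger readings are tempting, and the article does not support them.

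- **That the plan will create scores for the dead.** This is an inference. The sentence stands among general remarks on description and software, and could be meant for covariates or questionnaire items. It does not define a score after death as missing. What stands is that the rule is unqualified where death is a large, foreseeable reason for absent QoL forms.
- **That QoL rests on at most one questionnaire.** Step 1 counts only scheduled follow-up forms in the stated window. Routine forms may exist before and after it, a series could begin near entry, and the timeline figure is not shown. Against this, Recruitment and study procedures lists treatment, sedation or euthanasia and survival as the data drawn from patient files, and nowhere says that QoL forms outside the window will be analysed. The two Timeline figures still need reconciling.
- **That QoL will be compared by an unadjusted two-sample test.** The article says only that various tests will be used. A full protocol or analysis plan may name a model, and leaving that detail out of an article is no fault. What stands is that the article itself places the measurement after the intervention and confines adjustment to other outcomes.
- **That the primary outcome is compromised in the same way.** Deaths by week 2 are about 6% (4.5% to 10.1% for medians of 3 to 7 months), and probably fewer among patients well enough to consent after counselling.

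The same selection could lower the QoL figures, because the five-month median describes the background population and not the participants. The direction and size of any bias also depend on an imputation model that is not shown.

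A linear mixed model is not a sufficient answer: under its usual missing-at-random reading it also extrapolates trajectories past death. The choice of model and of a key QoL domain can be left to the analysis plan.

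**Conclusion.** The point holds in limited form. The imputation rule as stated permits QoL scores for deceased patients because it does not distinguish death from non-response. With a five-month median and an exponential curve, this concerns about 17% of patients at week 6 and 23% at week 8, with 13% to 35% across medians of 3 to 7 months. These figures rest on the assumed curve, on a clock starting at counselling, and on participants dying at the background rate.

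No QoL baseline or adjusted QoL analysis is stated for cohorts that are sequential and not randomised, although the form is in routine use. The active window and the questionnaire interval do not fit together as a repeated schedule.

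The weight falls on a secondary outcome. The changes are worth making before analysis, but the article does not show that the primary comparison is materially affected.

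**What to change.** 1. Restrict multiple imputation of QoL, and for consistency of the DCS, to patients alive at the scheduled assessment. Interpret the QoL comparison as one while alive, and report deaths by cohort beside it.
2. Use the routine QLQ-C15-PAL forms in Healthcare Monitor where consent covers them. Adjust the QoL comparison for the form nearest the palliative-trajectory visit, and record its date, since a form completed after counselling may already reflect it.
3. Reconcile the 1–2 month active window with the 6–8 week interval, and say which QoL forms enter the comparison.

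The cost is a few sentences of analysis wording and an extract of questionnaires already collected. The QoL estimate then applies only to patients while alive, so it must be read with the deaths. Some patients may lack a baseline form, and consent may not reach all later routine forms.

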### Methods/design

We will set up a single centre prospective sequential trial with two cohorts in a palliative HNSCC patient population. This study design is chosen in favour of a randomized controlled trial, because potential bias can be avoided as doctors develop a learning curve while working with the palliative model and could change their way of counselling. We aim to investigate the difference in effect of (prognostic) counselling without and with the use of OncologIQ Palliative by obtaining outcomes on decisional conflict, the amount of palliative treatment, palliative sedation or euthanasia, overall survival and QoL. The two cohorts in this study will be divided based on the type of prognostic counselling received. Cohort 1 will consist of patients who receive prognostic counselling without the model, reflecting the current clinical practice. Cohort 2 will comprise patients who receive additional prognostic counselling with the model. Additionally, we will conduct a qualitative evaluation through interviews among patients in cohort 2. This evaluation aims to investigate satisfaction with proactive care planning, including end-of-life discussions on preferred place of death and wishes for palliative sedation and euthanasia, following counselling with the use of OncologIQ Palliative.

Our hypothesis is that sharing personalized prognostic information on life expectancy with HNSCC patients in the palliative phase will empower patients throughout the decision-making process from the start of the palliative trajectory till death. More specifically providing this individualized prognostic information with the help of our prognostic model will lead to less decisional conflict and more satisfaction with the decision-making process. Additionally, we anticipate greater satisfaction with proactive care planning, including end-of-life discussions on preferred place of death and wishes for palliative sedation and euthanasia. Furthermore, when patients are optimally informed, they may choose palliative treatments less often, and it could lead to a higher QoL.

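### The between-cohort tests are unadjusted in a non-randomised sequential design, and the planned regression models are not given the job of estimating the cohort effect, so measured case-mix differences can be read as the effect of the model

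*Protocol article*

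**What the plan says.** All references are to the protocol article.

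- **Design (Methods/design).** "We will set up a single centre prospective sequential trial with two cohorts in a palliative HNSCC patient population". On randomisation: "This study design is chosen in favour of a randomized controlled trial". The reason given is "because potential bias can be avoided as doctors develop a learning curve while working with the palliative model".
- **Primary comparison (Statistical analysis, Clinical study).** "The differences between control (cohort 1) and intervention group (cohort 2) will be tested by a T-test if the data is normally distributed". A rank test is the fallback, again without covariates: "If the data is not normally distributed, the Mann-Whitney U test will be used".
- **Dichotomised DCS (same section).** The proportion with a score of 25 or more is compared "between cohort 1 and 2 using the chi-square test".
- **Survival (same section).** Kaplan-Meier curves per cohort, then: "Statistical significance will be assessed using the log-rank test".
- **Regression (same section).** "We will assess the independent contributions of potential influencing factors, such as smoking behaviour, level of education, marital status, age, WHO-performance status, and tumour characteristics", by multivariable regression for total DCS and Cox regression for survival. The stated aim is to relate patient characteristics to the outcome.
- **Baseline data (Recruitment and study procedures, Clinical study).** Smoking, ACE-27 and WHO performance status are given as examples of the patient and tumour characteristics recorded at baseline.
- **Entry to cohort 2 (same section).** Patients may decline an individual prognosis. Only those who were counselled with the model are then told about the study. Nothing comparable applies in cohort 1.

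**The concern.** Without randomisation, a two-group test compares the patients of two periods as well as two ways of counselling. If the cohorts differ in performance status, comorbidity, education or tumour characteristics, and those relate to decisional conflict or survival, the difference passes straight into the test result. The protocol plans the kind of model that could deal with the measured part of this, but gives it another purpose. If the t-test and the regression disagreed, the text would leave the unadjusted p-value as the answer on the primary outcome.

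The entry rule for cohort 2 makes non-comparability more likely. Those patients have chosen to hear an individual prognosis, a preference that could plausibly relate to decisional conflict, whereas cohort 1 mixes patients who would and would not have chosen it.

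A secondary point is the choice of test by a look at the distribution. The sample size rests on a difference in means of 8 points. Mann-Whitney tests a different quantity, so the data would decide what is being tested, and neither test can carry covariates.

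**Working it through.** **Inputs.** From Sample size and power calculations, Clinical study: difference 8, SD 17, α 0.05 (taken as two-sided; the article does not say), power 0.80, 79 needed and 80 planned per cohort. The imbalances below are assumptions, because the documents give none.

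**1. The plan's own figure.** n per group = 2 × (1.96 + 0.8416)² × 17² / 8² = 2 × 7.849 × 289 / 64 = 70.9, so 71; with the t distribution, 72. The stated 79 is not reproduced from the stated inputs; an unstated 10% allowance would give it (71 / 0.90 = 78.9). The gap is conservative and does not bear on this point. At 80 per cohort the power of the t-test is 84%.

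**2. False positives of the unadjusted t-test when there is no true effect.** SE = 17 × √(2/80) = 2.69. With 158 degrees of freedom the critical value is 1.975, so an observed difference of 1.975 × 2.69 = 5.3 points is significant. If case mix alone shifts the cohort difference by b points, the test statistic is noncentral t with noncentrality b / 2.69:

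| Assumed bias b (DCS points) | Noncentrality | P(significant) |
|---|---|---|
| 1 | 0.37 | 6.6% |
| 2 | 0.74 | 11.5% |
| 3 | 1.12 | 19.9% |
| 4 | 1.49 | 31.6% |
| 5 | 1.86 | 45.6% |

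A bias of 2 to 4 points is a quarter to a half of the 8-point target effect.

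**3. What adjustment does for a measured confounder.** Simulation: 10,000 runs, 80 per cohort, one binary factor, overall SD about 17, no true effect. Bias = difference in prevalence × DCS gap between levels of the factor.

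| Prevalence, cohort 1 / cohort 2 | DCS gap | Bias | Unadjusted | Adjusted |
|---|---|---|---|---|
| 40% / 40% | 10 | 0 | 5.0% | 5.1% |
| 50% / 30% | 10 | 2 | 12.2% | 5.4% |
| 50% / 30% | 15 | 3 | 20.1% | 4.8% |
| 55% / 25% | 15 | 4.5 | 39.0% | 4.8% |

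Adjustment returns the rate to about 5%, for factors that are measured and in the model.

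**4. What adjustment costs in power.** With seven covariates, SE = 17 × √[(1 − R²y) / (1 − R²c)] × √(2/80) on 151 degrees of freedom. R²y is the share of DCS variance and R²c the share of cohort membership that the covariates explain. Power for 8 points:

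| R²y | R²c = 0 | R²c = 0.10 | R²c = 0.20 |
|---|---|---|---|
| 0 | 84% | 80% | 75% |
| 0.10 | 88% | 84% | 80% |
| 0.20 | 91% | 88% | 84% |

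Where the covariates explain at least as much of cohort as of DCS, power lies between 75% and 84%. The higher values need covariates that explain DCS better than they explain cohort.

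**The case against.** The strongest reply is that adjusted models are already in the plan. The regression text is open-ended, its covariates are examples, and neither cohort nor ACE-27 is excluded; the exact model terms may sit in a fuller document. Variables are also to be described by cohort, so measured imbalance would be visible. This stands against any reading that the plan has no adjustment or has left ACE-27 out. It does not meet the point made here: the article itself names the tests of the cohort difference, and gives the regression a different purpose.

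A reader might infer more than the text supports in several other ways:

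- **That the result will be biased.** No imbalance can be derived from the documents. The false-positive rates show sensitivity; they are not a forecast.
- **That regression would remove period effects.** Calendar time is almost fully aliased with cohort, so it would not.
- **That adjustment would raise power.** That needs covariates largely unrelated to cohort, which sits badly with their being confounders. The case for adjustment is bias.
- **That switching to Mann-Whitney is without benefit.** The article names no normality test and gives no DCS distribution, so this cannot be shown. What stands is the change in the quantity tested.
- **That Methods/design claims freedom from confounding.** Its argument concerns physicians learning from the model and changing how they counsel, which is contamination. It is silent on case mix and period.
- **That every outcome is fixed to an unadjusted test.** For palliative treatment and quality of life the article names no specific test.

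**Conclusion.** The point holds. In a non-randomised sequential comparison, the article fixes unadjusted tests for the primary DCS score, for DCS ≥ 25 and for survival, and does not give the planned multivariable models the task of estimating the cohort effect. Followed as written, the plan can present measured case-mix differences as an effect of counselling with the model, and the one-sided entry filter on cohort 2 makes such differences more likely.

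The size depends on an imbalance that is unknown. Under assumed biases of 2 to 4 points, with SD 17, 80 analysable patients per cohort and no true effect, the false-positive rate is about 11% to 32%. Adjustment restores about 5% for measured confounders only; calendar period stays inseparable from cohort, and self-selection into cohort 2 is only partly addressed by baseline covariates. Because this governs the primary result, it should be settled before outcomes are compared.

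**What to change.** 1. Make the planned linear regression of total DCS the primary analysis, with cohort as a named term and robust standard errors. Fix the covariates before outcomes are compared: age, education, marital status, smoking, WHO performance status, ACE-27 and tumour characteristics. Report the adjusted mean difference with its 95% confidence interval. This matches the 8-point mean difference behind the sample size and removes the distribution-dependent switch of test.
2. Use cohort plus the same covariates in logistic regression for DCS ≥ 25 and in Cox regression for survival.
3. Keep the t-test or Mann-Whitney, chi-square and log-rank tests as supportive.
4. State as limitations that calendar period is aliased with cohort and that baseline covariates only partly deal with opt-in selection into cohort 2, and word the conclusions to match.

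**Cost.** A change of wording only; every covariate is already named in the article and no extra patients are required. A few degrees of freedom are used, and some power may be lost if the covariates are related to cohort (75% to 84% in the scenarios where they explain cohort at least as well as DCS). No gain in power should be claimed.
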